### Trial treatments

#### Details of the study treatment.

Subjects who meet the inclusion criteria above and do not meet any exclusion criteria will initiate either a combination therapy with filgotinib 200 mg/day (or 100 mg/day if estimated glomerular filtration rate is below 60 mL/min/1.73 m²) and MTX (Add-on group) or filgotinib monotherapy (Switch group) after completing the baseline assessment (week 0). bDMARDs and csDMARDs other than MTX must be discontinued at the start of filgotinib administration. In the Add-on group, MTX should be maintained at the same dose as at enrollment until week 24 unless clinically significant adverse events occur. After week 24, patients in the Add-on group may reduce or discontinue MTX, while patients in the Switch group may resume MTX administration if desired by the patient and agreed upon by the attending rheumatologist.

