The rate of CRRP and RRP at week 24 and week 48 will be analyzed. The denominator for the proportion will be the number of FAS in each group, with the numerator for the CRRP rate being the number of cases with an mTSS increase of 3 or more at week 24 and 48, and the numerator for the RRP rate being the number of cases with an mTSS increase of 5 or more at week 24 and 48.

8) Cumulative values of CRP and matrix metalloproteinase (MMP)-3

The cumulative values of CRP and MMP-3 will be analyzed, with definition as the area under the curve (AUC) for CRP and MMP-3 for each subject.

9) Work productivity and activity impairment (WPAI)

WPAI at week 24 and week 48 will be analyzed. At week 24, summary statistics will be calculated for baseline values, measurements at each time point (week 24 and week 48), and changes from baseline in the two groups (Add-on group and Switch group). At week 48, the analysis will include four groups (Add-on to Switch group and Switch to Add-on group in addition to the original two groups).

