#### Safety endpoints.

Number of cases and incidence rate of adverse events, clinical laboratory values, and vital signs will be recorded from the first dose until week 48 of study treatment initiation. An adverse event is any undesirable symptom, sign, disease, or abnormal clinical laboratory value that occurs in a subject, regardless of whether there is a causal relationship with the study. Worsening of arthritis is considered an insufficient effect of the study treatment and will not be classified as an adverse event. The principal investigator and others will assess the severity of adverse events in three categories (mild, moderate, and severe). The severity of adverse events (mild, moderate, and severe) will be assessed based on the Common Terminology Criteria for Adverse Events (CTCAE). This assessment of severity is different from the evaluation of the seriousness of the adverse event. A serious adverse event is an adverse event that results in death, is life-threatening, requires hospitalization or prolongation of an existing hospitalization, leads to permanent or significant disability or dysfunction, or causes congenital abnormalities in offspring. On the other hand, hospitalizations without adverse events will not be considered serious adverse events if they fall under the following categories:

1) Hospitalizations for purposes other than the treatment or evaluation of an adverse event (e.g., health checkups).2) Hospitalizations for scheduled surgeries or examinations planned before informed consent, provided there is no change in the patient’s condition after initiating the study treatment.3) Hospitalizations required for the administration of the study drug.4) Hospitalizations for the periodic maintenance of pre-existing medical devices (e.g., battery replacements).

Each investigator will make determinations based on these predefined criteria.

All adverse events must be followed up for 28 days after the completion of study treatment or until recovery, whichever comes first. Additionally, serious adverse events must be followed up until they resolve or, if resolution is not expected, until the symptoms stabilize. However, if it is medically determined that follow-up is not necessary, the follow-up for the adverse event may be discontinued.

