For the safety analysis, treatment-emergent adverse events (TEAEs) observed during the period from the start of the study treatment to the end of the observation period will be summarized. Adverse events that cannot be ruled out as being causally related to the study treatment will be classified as adverse drug reactions. For each group, the number and percentage of cases of TEAEs and adverse drug reactions will be summarized by system organ class and preferred term. Additionally, a summary by severity level will also be provided.

Missing data at each time point will not be imputed. For patients who discontinue the study, only the data obtained up to the point of discontinuation will be used for analysis. Additionally, when analyzing the proportion of patients who achieve the endpoint, cases with missing data at each time point, including those who discontinued the study, will be considered as non-responders and included in the denominator.

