## Discussion

The FAITHFUL study protocol outlines a comprehensive investigation into the efficacy and safety of filgotinib monotherapy versus combination therapy with MTX in patients with rheumatoid arthritis who have shown inadequate response to MTX. Such direct comparisons are currently lacking in the literature, as acknowledged in the protocol. Therefore, this study design reflects current challenges in managing rheumatoid arthritis, such as balancing therapeutic efficacy and minimizing adverse effects.

In the FINCH3 trial, the only study comparing filgotinib plus MTX, filgotinib monotherapy, and MTX monotherapy in MTX-naive patients, adverse events up to week 24 were observed in 66.1% (275/416) of patients in the filgotinib 200 mg plus MTX group, 69.6% (144/207) in the filgotinib 100 mg plus MTX group, 55.7% (117/210) in the filgotinib 200 mg monotherapy group, and 63.2% (263/416) in the MTX monotherapy group [9]. Although no statistical tests were conducted, there was a tendency for higher rates in the filgotinib plus MTX groups compared to the filgotinib monotherapy group. Among the major adverse events, the frequency of nausea was 10.3% (43/416) in the filgotinib 200 mg plus MTX group, 15.5% (32/207) in the filgotinib 100 mg plus MTX group, 6.2% (13/210) in the filgotinib 200 mg monotherapy group, and 10.8% (45/416) in the MTX monotherapy group, indicating a trend toward higher rates in the MTX combination groups. Thus, if the FAITHFUL study demonstrates the non-inferiority of filgotinib monotherapy compared to filgotinib plus MTX combination therapy, it could serve as evidence for a treatment approach with equivalent efficacy and fewer adverse effects in the future. This would contribute to establishing a more appropriate treatment strategy for patients with rheumatoid arthritis with insufficient response to MTX.

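### The only stated adverse-event summary runs to week 48, past the week-24 point after which both arms may change MTX, so it dilutes the randomised safety contrast to the extent that patients do change

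*Protocol article*

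**What the plan says.** Under Statistical methods, the safety analysis is set as follows: "treatment-emergent adverse events (TEAEs) observed during the period from the start of the study treatment to the end of the observation period will be summarized". The layout is by arm: "For each group, the number and percentage of cases of TEAEs and adverse drug reactions will be summarized by system organ class and preferred term", with a further summary by severity. The end of the observation period is not defined there, but Safety endpoints says that adverse events, laboratory values and vital signs "will be recorded from the first dose until week 48 of study treatment initiation".

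The MTX contrast has a shorter life. Details of the study treatment keeps the Add-on dose fixed to week 24, apart from clinically significant adverse events, and then allows change in both arms: "patients in the Add-on group may reduce or discontinue MTX, while patients in the Switch group may resume MTX administration". Trial design and the Fig 2 legend say the same.

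Two other places bear on this. For WPAI, the Secondary endpoints section states: "At week 48, the analysis will include four groups (Add-on to Switch group and Switch to Add-on group in addition to the original two groups". And the Discussion says that if non-inferiority is shown, "it could serve as evidence for a treatment approach with equivalent efficacy and fewer adverse effects in the future".

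**The concern.** The Introduction gives the reason for the trial: filgotinib without MTX is expected to be safer while efficacy is maintained. The safety question is therefore what happens to adverse events when MTX is dropped. Randomisation answers that directly up to week 24. After week 24 the arms can become more alike in MTX exposure, and the patients who change are chosen by a shared decision that may depend on response and tolerance.

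A single cumulative percentage per arm to week 48 cannot separate the two periods. If MTX raises adverse-event rates, as the article supposes, changes in either arm pull the percentages together. The primary efficacy endpoint is at week 24, and so are the FINCH3 adverse-event rates that the Discussion cites in support. The efficacy sensitivity analyses are tabulated by treatment period, and WPAI is regrouped after week 24. The adverse-event summary has no such break.

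At stake is whether the main safety table answers the trial's safety question, and whether a later statement about fewer adverse effects has an estimate behind it.

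**Working it through.** **Inputs from the article**
- Any adverse event to week 24 in FINCH3 (Discussion): 275/416 with filgotinib 200 mg plus MTX, and 117/210 with filgotinib 200 mg alone.
- Nausea in the same arms: 43/416 and 13/210.
- Planned size: 60 per arm (Sample size calculation).

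**Assumptions, not in the article**
- The FINCH3 rates, from MTX-naive patients, carry over to this population.
- Hazards are constant within each MTX state.
- A share *f* of each arm takes on the other arm's hazard at week 24. No share is given, so a range is shown.

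**Reproducing the quoted figures.** 275/416 = 66.1% and 117/210 = 55.7%, a difference of 10.4 points. 43/416 = 10.3% and 13/210 = 6.2%. All match. The article states no sample size or power for safety.

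**Model.** The 24-week event-free proportions are a = 1 − 0.661 = 0.339 (Add-on) and s = 1 − 0.557 = 0.443 (Switch). At 48 weeks:
- Add-on risk = 1 − a × [(1 − f)a + f s]
- Switch risk = 1 − s × [(1 − f)s + f a]
- Difference = (1 − f)(s² − a²), because the cross terms cancel.

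Here s² − a² = 0.196 − 0.115 = 0.081.

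| Share changing in each arm | Add-on, week 48 | Switch, week 48 | Difference (points) |
|---|---|---|---|
| 0% | 88.5% | 80.4% | 8.1 |
| 20% | 87.8% | 81.3% | 6.5 |
| 30% | 87.5% | 81.8% | 5.7 |
| 50% | 86.8% | 82.7% | 4.1 |
| 100% | 85.0% | 85.0% | 0 |

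**Separating two effects.** The drop from 10.4 points at week 24 to 8.1 at week 48 with nobody changing is 2.3 points. It arises because most patients in both arms will have had some event by then. Dilution is only what is lost below 8.1: 1.6 points at 20% and 4.0 (8.12 − 4.06 before rounding) at 50%.

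**A less common event.** For nausea the ceiling hardly matters. The risk ratio is 1.67 at week 24 and, at week 48, 1.63 with no change, 1.48 with 20% changing and 1.27 with 50%.

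**Precision with 60 per arm at week 24.** SE = √(0.661 × 0.339/60 + 0.557 × 0.443/60) = 0.0886, so the 95% half-width is 1.96 × 0.0886 = 0.174, about 17 points.

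**The case against.** The best reply is that a whole-period safety table by randomised arm is ordinary practice and correctly describes the two strategies, including the MTX choices that follow. That stands, and the table should stay. It is also fair that a statistical analysis plan could add a week-24 table or a risk difference, so the absence of a stated between-arm estimate is not itself an error. But the article does more than leave the window open. It names one, and that window outlasts the contrast that the safety rationale is about.

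Several stronger readings are tempting and not supported.

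- **That the contrast will be diluted by a known amount.** If nobody changes MTX there is no dilution. The shares above are assumed, and the model treats every change as complete, whereas Add-on patients may only reduce the dose.
- **That low power shows the window to be wrong.** For 66.1% against 55.7% with 60 per arm, power is about 21% (two-sided 5%). That is the week-24 contrast, so it applies equally to the table proposed here. The article claims no safety test.
- **That WPAI loses its randomised comparison at week 48.** The same item also lists week-48 measurements and changes for the two arms. The wording is unclear, and only summary statistics are named.
- **That the Discussion draws a safety conclusion from DAS28-CRP as a rule.** The sentence is hedged, and it follows an acknowledgement that the FINCH3 rates were not tested. It is loose, because non-inferiority on DAS28-CRP says nothing about adverse events, but it is not a decision rule.

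Nor is the period before week 24 perfectly protected: Add-on MTX may change for clinically significant adverse events. That is part of the randomised treatment as assigned.

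**Conclusion.** The point holds in limited form. The one adverse-event window that the article states runs about 24 weeks beyond the period in which the MTX difference is maintained, and it answers the safety question less well than a week-24 comparison would. On the assumptions above, changes by 20% to 50% of each arm would take the 48-week any-event difference from 8.1 points to between 6.5 and 4.1. The direction rests on the article's own premise that MTX adds adverse events; the size rests on an unknown share and on rates from MTX-naive patients. Against a confidence interval of about ±17 points these shifts are modest. The case for change is that the comparison should match the question, at almost no cost, rather than that the trial's safety findings would be invalid. The primary efficacy analysis is untouched.

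**What to change.** 1. Make treatment-emergent adverse events and adverse drug reactions from first dose to week 24, by randomised arm, the main comparative safety table, with risk difference and 95% CI. Fix the cut in advance, since the week-24 visit may fall up to 2 weeks either side.
2. Show weeks 24 to 48 separately, by randomised arm.
3. Keep the whole-period table, described as a summary of the two strategies including later MTX choices.
4. Label any table by MTX actually taken after week 24 as descriptive and non-randomised. This includes the four-group WPAI table, beside which week-48 WPAI should clearly be given for the two randomised arms. Confirm first that dates of MTX changes are captured; the article does not say so.
5. Reword the Discussion so that any statement about fewer adverse effects rests on the estimated safety difference and its interval, and efficacy is described as non-inferior within 0.6.

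The cost is one extra set of tables and a more modest safety statement. Treatment rules, visits and sample size do not change. Data fix is planned for March 2027, and the change should be written down before then.

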### Ethics and dissemination

#### Ethical approval.

The study has been approved by the Certified Review Board of Keio University Hospital (N20230002), and conforms to the Declaration of Helsinki and good clinical practice guidelines. Written informed consent is obtained from participants prior to enrollment. Any significant modifications to the study protocol must receive approval from the Certified Review Board of Keio University Hospital.

#### Informed consent.

The principal investigator and other study personnel will provide appropriate and sufficient explanations using written documents. The explanation documents will be written in simple language that the participants can understand, and will be used after obtaining the opinion of the Certified Review Board of Keio University Hospital and the approval of the institutional administrator. The documents will be appropriately version-controlled. The written and oral explanations will include the purpose, methods, anticipated outcomes, risks, and potential disadvantages of the study, as well as the fact that participation is voluntary, that refusal to participate will not result in any disadvantage, and that participants can withdraw their consent at any time.

Informed consent will be confirmed by the participant signing the consent document. The distribution and storage methods of the consent document will follow the procedures of each institution. If new information regarding efficacy, safety, or other aspects of the study that could affect the participant’s consent is obtained, or if there are changes to the study protocol that could influence consent, the participant will be promptly provided with updated information.

#### Confidentiality.

Data related to subjects enrolled in this study will be coded using the registration number issued at the time of enrollment and entered into the EDC system. Personal information that can directly identify subjects, such as names, addresses, or phone numbers, will not be recorded in the database. Furthermore, any information related to subjects’ privacy obtained during the study will not be disclosed to third parties by study personnel.

#### Dissemination plan.

The total study duration is expected to be 3 years and 6 months, with the study scheduled to conclude in September 2027. Data from all centers will be analyzed collectively and the results of this study are planned to be submitted for presentation in scientific conferences and publication in relevant peer-review journals.

### Study discontinuation criteria

The study will be discontinued if any of the following criteria are met. The principal investigator will promptly inform the principal investigators at each participating medical institution about the decision to discontinue the study. Each principal investigator will promptly notify the subjects and take appropriate medical interventions and other necessary actions.

1) If the number of enrolled subjects is significantly below the target, or if frequent deviations from the study protocol occur, making it difficult to complete the study2) If a serious adverse event is reported and it is determined that there are safety concerns regarding the protocol treatment3) If new information related to the protocol treatment is obtained, such as from publications or conference presentations, and it is determined that there are safety concerns regarding the protocol treatment

## Discussion

The FAITHFUL study protocol outlines a comprehensive investigation into the efficacy and safety of filgotinib monotherapy versus combination therapy with MTX in patients with rheumatoid arthritis who have shown inadequate response to MTX. Such direct comparisons are currently lacking in the literature, as acknowledged in the protocol. Therefore, this study design reflects current challenges in managing rheumatoid arthritis, such as balancing therapeutic efficacy and minimizing adverse effects.

In the FINCH3 trial, the only study comparing filgotinib plus MTX, filgotinib monotherapy, and MTX monotherapy in MTX-naive patients, adverse events up to week 24 were observed in 66.1% (275/416) of patients in the filgotinib 200 mg plus MTX group, 69.6% (144/207) in the filgotinib 100 mg plus MTX group, 55.7% (117/210) in the filgotinib 200 mg monotherapy group, and 63.2% (263/416) in the MTX monotherapy group [9]. Although no statistical tests were conducted, there was a tendency for higher rates in the filgotinib plus MTX groups compared to the filgotinib monotherapy group. Among the major adverse events, the frequency of nausea was 10.3% (43/416) in the filgotinib 200 mg plus MTX group, 15.5% (32/207) in the filgotinib 100 mg plus MTX group, 6.2% (13/210) in the filgotinib 200 mg monotherapy group, and 10.8% (45/416) in the MTX monotherapy group, indicating a trend toward higher rates in the MTX combination groups. Thus, if the FAITHFUL study demonstrates the non-inferiority of filgotinib monotherapy compared to filgotinib plus MTX combination therapy, it could serve as evidence for a treatment approach with equivalent efficacy and fewer adverse effects in the future. This would contribute to establishing a more appropriate treatment strategy for patients with rheumatoid arthritis with insufficient response to MTX.

The study protocol defines multiple efficacy endpoints, including DAS28-CRP changes, ACR response rates, quality-of-life measures such as HAQ and WPAI, and radiological changes, indicating a comprehensive endpoint design. Safety endpoints are also robust, emphasizing AEs and laboratory abnormalities. Furthermore, allowing shared decision-making between patients and rheumatologists post-week 24 reflects a patient-centric approach, providing flexibility in tapering or restarting MTX based on clinical need. On the other hand, the limitation of this study is the lack of blinding which may introduce bias in subjective endpoints like patient-reported outcomes. However, this open-label design allows for a more practical evaluation of treatment effectiveness in a real-world setting, where patients and physicians are aware of the treatments being administered, potentially enhancing adherence and capturing a broader range of patient experiences.

In clinical trials, outcome measures are often repeatedly assessed in the same individuals over time, resulting in longitudinal data. However, it is common for participants to discontinue the study or miss scheduled visits, leading to incomplete or missing data. MMRM is a likelihood-based approach that provides valid estimates under the assumption of missing at random (MAR), without requiring data imputation. MMRM utilizes available data while accounting for baseline covariates and within-subject correlations, making it a robust method when the mean and covariance structures are correctly specified. However, as the missing data mechanism cannot be directly verified from observed data, and MMRM is only valid under MAR, it is important to consider alternative analytical approaches when its assumptions are not met. In this study, we acknowledge these limitations and will explore additional sensitivity analyses to ensure the robustness of our findings.

In conclusion, the FAITHFUL study protocol is well-designed to address an important clinical question in the management of rheumatoid arthritis. By leveraging a randomized, multicenter approach, the study could provide pivotal evidence on the viability of filgotinib monotherapy as an effective alternative for MTX-refractory patients.
